## 1. Objectives

- 1.1 Primary: To measure gene expression in normal prostate tissue acquired by needle biopsy in men assigned to placebo, lycopene or fish oil nutritional supplements at baseline and after intervention. The primary outcome measure is a two-fold decrease in mRNA transcript level. The primary study endpoint is the difference in the proportion of the patients in a nutritional supplement arm compared to a placebo control arm achieving a two-fold decrease in the gene of interest. Quantitative polymerase chain reaction will assess modulation of expression of the *insulin-like growth factor 1 (IGF1)* and the cyclooxygenase 2 (*Cox-2*) gene in lycopene and fish oil recipients respectively.
- 1.2 Secondary: We will use cDNA microarrays with 30,000 independent clones to identify new candidate molecular targets for lycopene and omega-3 response pathways deserving further study.
- 1.3 Secondary: To correlate baseline gene expression patterns determined by cDNA array analysis with self-reported dietary intake. Based on previous epidemiologic, *in vitro*, and *in vivo* studies, we hypothesize that higher intake of total energy, fat/meat/animal products, dairy/calcium, and lower intakes of fish, vegetables, tomatoes/lycopene, vitamin E, and selenium will be associated with particular gene expression profiles.
- 1.4 Secondary: We will assess if there are gene expression patterns correlated with progression or lack of progression as assessed at a time point 12 months after study entry.
- 1.5 Secondary: We will assess if lycopene or omega-3 supplements affect the incidence of tumor progression.

## **2. Background**

### **2.1 Scientific background**

Prostate-specific antigen (PSA) screening has resulted in dramatic improvements in early detection and treatment of prostate cancer. However, the natural history of the disease may be protracted, and all available treatments potentially exert a significant negative impact on patient quality of life. In the Molecular Effects of Nutrition Supplements (MENS) trial, men with favorable-risk prostate cancer, who opt initially for watchful waiting, will be offered participation in a prospective randomized placebo- controlled 3-month nutritional intervention study with a genetic correlative science outcome, using supplementation with lycopene or fish oil as a possible means to modulate prostate cancer progression. Research needle biopsies will be taken at the beginning of the study and after intervention. The primary outcome measure is a two-fold up or two-fold down change in gene transcript level between three-month and baseline biopsies in normal prostate tissue. In particular, we hypothesize that lycopene supplementation will be associated with decreased expression of the *insulin-like growth factor (IGF)* gene, and that fish oil supplementation will be associated with down-regulation of the *Cox-2* gene at 3 months. Furthermore, we will identify new candidate molecular targets for lycopene and omega-3 response pathways deserving further study since microarrays will be used to assess an additional 30,000 genes for each study biopsy.

### **2.2 Diet and prostate cancer**

Several food and nutrients have been studied in relation to prostate cancer. In particular, lycopene/tomato products, fish, vitamin E, selenium, total and specific vegetables, and soy/legumes have been routinely inversely associated with risk of prostate cancer in observational studies or clinical trials. Vitamin E and selenium are currently being examined in a large clinical trial for the primary prevention of prostate cancer (SELECT trial). While total and specific vegetables and soy/legumes have been associated with a reduced risk of prostate

cancer incidence, food-based interventions cannot be blinded and “greater vegetable intake” represents a multitude of nutrients and phyto-chemicals that may influence and interact with many genetic pathways. Attempting to study many nutrients and pathways simultaneously can inhibit the ability to identify any one single pathway. Thus, we chose to focus our study on elucidating the molecular effects of lycopene and fish oil in a randomized, double-blinded, placebo-controlled clinical trial among men with prostate cancer. We will stratify patients with regards to baseline intake of fish and tomato products before randomization, to ensure that men in both experimental arms are a balanced sample of the study population. Below, we outline the evidence supporting the beneficial effects of lycopene and fish oil. We conclude this section with an overview of other dietary risk factors for prostate cancer that we will investigate in an exploratory fashion by comparing the self-reported diet records and questionnaire data with different molecular and genetic markers/indices.

## **2.3 Lycopene/tomato products**

### **General**

Lycopene, most commonly found in tomatoes, is the most efficient quencher of singlet oxygen among the common carotenoids [1] and is the predominant carotenoid in plasma [2] [3] and various tissues [4], including the prostate gland [5]. The Health Professionals Follow-up Study found that high lycopene intake was correlated with a 21 percent lower risk of prostate cancer; and tomato sauce, the major predictor of serum lycopene levels, was the strongest dietary predictor of reduced prostate cancer risk (36% reduction for high versus low intake) [6]. This relationship was independent of other factors and stronger for advanced cases. Two studies of pre-diagnostic serum carotenoids and prostate cancer observed inverse associations for lycopene. The Physicians Health Study found that being in the fifth vs. the first quintile of plasma lycopene levels was associated with an approximate 25% reduction in overall prostate cancer risk, and a 44% statistically significant reduction in risk of aggressive cancer [7]. Lycopene levels in

African American men are lower than in Caucasian men, paralleling the difference in prostate cancer incidence seen in these two groups[8].

Is the lycopene itself protective, or is it merely a marker for some other diet or behavioral trait? Recently, investigators reported statistically significant reductions in levels of DNA oxidative damage and PSA before and after intervention with a tomato sauce-based (lycopene-rich) diet given three weeks prior to prostatectomy among 30 prostate cancer patients [9]. In addition, one recent study compared 15 men taking 30mg lycopene supplement for three weeks with 11 men given no intervention, who then underwent radical prostatectomy [10]. In this study, both decreased tumor volume and decreased incidence of high grade prostate intraepithelial neoplasia (PIN) were found. A Southwest Oncology Group Trial is planned to confirm these findings. In addition, a case report details the benefit of lycopene in a patient referred to hospice care after failure of cytotoxic chemotherapy. The patient reported taking both lycopene supplements and saw palmetto as alternative medicines and achieved a lasting complete remission of his advanced prostate cancer[11]. Given these findings, which show that lycopene itself has protective effects, we hypothesize that lycopene will have a distinct gene expression signature in prostate tissue.

The molecular mechanism of lycopene action on target cells is unknown, and may extend beyond quenching oxygen free radicals. Breakdown of any carotenoid, including lycopene, results in the generation of vitamin A and other retinoids. Recently, prostate short chain dehydrogenase/reductase was found to be specifically a retinal reductase, indicating that prostate tissue may have a unique metabolism of retinoid molecules[12]. Furthermore, lycopene[13], or acyclo-retinoic acid, one of the products of lycopene metabolism, was shown to cause prostate cells to undergo apoptosis *in vitro*[14]. Thus, the molecular mechanism of lycopene action may include induction of the apoptotic cascade. In addition, lycopene supplementation was associated with a decrease in serum levels of insulin-like growth factor I (IGF-1) in two recent small trials[15, 16]. Serum IGF-I has been linked to greater risk of prostate cancer in several studies, including two conducted by our group ([name] et al, Science 1998, [name] et al,

JNCI, 2002). Since IGF modulates the protein kinase B/Akt kinase pathway critical to prostate cell survival[17, 18], a reduction in IGF levels would be expected to promote apoptosis in prostate cancer. The cDNA arrays we will use in our study (see Sections C and D, preliminary data and research methods), include sequences encoding the prostate short chain reductase gene, the retinoic acid receptors, apoptotic mediators and components of the IGF signaling pathway, to maximize the chance to detect the *in vivo* mechanism of lycopene action on the prostate.

### **Pharmacokinetics**

Lycopene, a non provitamin A carotenoid, can act directly as an antioxidant[19]. At lycopene levels readily achieved in humans, glutathione transferase and superoxide dismutase activities are induced in animal models[20]. Small differences in bioavailability are seen depending on which type of oil emulsion is used as the vehicle in lycopene administration[21], and lycopene bioavailability is greatly enhanced by food processing, usually by making a tomato sauce[22].

### **Toxicology**

The toxicity of lycopene was determined in a thirteen week study of male and female Wistar rats fed several very large doses – 0, 500, 1500 and 3000 mg/kg[23]. No statistically significant, dose-related effects on body weight, body weight gain, food consumption, hematology, urinalysis, clinical chemistry or ophthalmoscopic parameters were seen in any of the lycopene product or lycopene formulation matrix groups in comparison to the vehicle control group. No deaths attributed to the test articles occurred during the study and the only clinical finding and at necropsy was the presence of red pigment in the feces and gastrointestinal tract that was associated with the red-pigmented test materials. Thus, there are no significant toxic findings even when lycopene is administered at very high dose levels[23]. Organ histology at the time of animal sacrifice was unchanged relative to controls.

## **Phase I trials**

Recently a small clinical study of 15 men assigned supplement and 11 controls showed a decrease in PSA, decrease in tumor volume and decrease in IGF-1 levels after 3 month consumption prior to radical prostatectomy surgery[16]. While this study is unique in that the population considered had prostate cancer, the many additional studies of lycopene consumption addressing cardiovascular, ocular or other clinical endpoints have not been complicated by any adverse effects[24-31]. Together these studies represent treatment of hundreds of subjects without ill effect.

## **2.4 Fish oil/omega-3 fatty acid**

### **General**

There is provocative evidence for a potential protective effect of fish intake on prostate cancer risk from a large U.S. cohort study [32], a Swedish case-control study [33], a smaller New Zealand case-control study[34], cross-sectional serum studies[35], and several experimental studies in prostate cancer cell lines[36]. DU-145 xenografts were growth inhibited in nude mice fed a diet rich in omega-3 fatty acids[37]. Furthermore, we have preliminary evidence from the Health Professionals Follow-up Study of a moderate to strong inverse association for post-diagnostic fatty fish intake and risk of prostate cancer recurrence/mortality (unpublished data, *[name]*). While this cohort was not specifically designed to study prostate cancer recurrence and mortality and has limited power to detect associations, we ([name] and colleagues at Harvard University) examined post-diagnostic diet relevant to pre-diagnostic diet and risk of prostate cancer recurrence and mortality among 1,584 incident prostate cancer cases, using prospectively collected questionnaire data. In a preliminary analysis, a positive change in intake of fish after diagnosis (e.g. consuming more fish after diagnosis relative to before diagnosis) was strongly protective for risk of prostate cancer recurrence (RR=0.35 for increasing intake by one serving/day,  $p = 0.0002$ ), independent of other food groups, PSA level at diagnosis, Gleason score of the tumor, stage, and primary treatment choice. Furthermore, the risk of dying from

prostate cancer was inversely associated with consuming more fish, grains, tomato products, and vegetables after diagnosis relative to prior to diagnosis, independent of baseline clinical characteristics.

### **Pharmacokinetics**

Omega-6 fatty acid, also known as arachidonic acid, is metabolized by the COX-2 enzyme to become prostaglandin E2 (PGE2), a molecule implicated in carcinogenesis in part due to its ability to stimulate prostate cell growth *in vitro*[38, 39]. Ratios of omega-3 to omega-6 fatty acid are thought to modulate COX-2 expression at both RNA and protein levels.

### **Toxicology**

The acute and chronic toxicity of dietary fish oil was determined in a twelve-month study of Sprague-Dawley rats fed chow equivalent to human consumption of nine grams fish oil daily. Expected decreases in serum triglyceride, total cholesterol and LDL levels were seen[40]. There were no acute or chronic differences in external appearance, level of activity, daily food consumption, blood cell counts, renal function, thyroid function, prothrombin time or activated partial thromboplastin time, and organ histology at the time of animal sacrifice was unchanged relative to controls.

### **Phase I trials**

Recently a small group of men were studied after three-month intervention comprised of low fat diet with fish oil supplementation. At the three-month assessment of these nine men, the ratio of omega3 to omega6 fatty acids in gluteal fat was increased, and COX-2 expression quantitated by PCR from prostate needle biopsies was decreased in four out of seven patients assessed[41]. While preliminary, these results indicate that fish oil rich in omega-3 fatty acids may influence prostate cancer progression. In addition, no ill effects were found in many additional clinical trials of a similar patient population when fish oil effects on atherosclerosis, or

other clinical endpoints were assessed[42-45]. The cited trials include studies in infants and pregnant women, which highlights the safety of treatment with fish oil as a nutritional supplement.

## **2.5 Clinical background: watchful waiting in prostate cancer**

Prostate cancer is the most common malignancy in men, with 221,000 new cases and 29,000 deaths expected in 2003[46]. Worldwide, incidence of prostate cancer diagnosis is increasing at 3% per year[47]. The advent of prostate specific antigen (PSA) screening has resulted in improvements in early diagnosis of prostate cancer. However, the natural history of the disease may be protracted and only 25-33% of men diagnosed with prostate cancer actually die of the disease[48, 49]. Moreover, available treatments all have a significant negative effect on quality of life[50]. Analysis of tumor registries in the United States[51] and Sweden[52] with fifteen year median follow-up shows that some patients enjoy prolonged survival without definitive treatment[51]. Low grade tumors, in particular, were associated with low 4-30% risk of death from prostate cancer. However, for 876 men with aggressive Gleason pathologic scores of 8 to 10, surgery or radiation provided better five-year overall rates than expectant management. In this US tumor registry study, the ten year prostate cancer specific survival for surgery was 67%, for radiotherapy 53%, and for expectant management 45% [53]. Since PSA screening has led to stage migration with patients often diagnosed with the earliest clinical stage T1c, interest has grown in offering **watchful waiting** – careful surveillance with frequent PSA testing followed by repeat biopsy and referral for definitive treatment when indicated – as an initial treatment recommendation.

A recent analysis of 4,458 men in the CaPSURE longitudinal, observational prostate cancer patient database found that 8.2% of patients, principally those who were older and had favorable risk characteristics, opted for watchful waiting; 52% of these patients underwent secondary treatment within five years, especially those who were younger or had higher PSA scores at diagnosis[54]. A single-institution study of 199 patients, again comprised of older

patients with low-risk tumors, showed that 44% of men underwent prostate cancer treatment by five years, with a disease-specific survival rate of 98% at seven years[55]. There is growing evidence that patients who choose watchful waiting do not experience adverse psychological impact, even when assessed with 10 year median follow-up[56].

To date, most patients opting for watchful waiting have been older, with more comorbidity, or strongly averse to extant treatment alternatives. Initial watchful waiting trials reported on study populations with high clinical T stage, PSA and Gleason scores, and found that several men developed metastasis during observation[57]. However, with the development of better monitoring algorithms, new trials are exploring the possibility of offering safe initial observation to greater numbers of patients. Those who have low-risk tumor characteristics could pursue a trial of initial active monitoring at the time of diagnosis, without sacrificing curative intent, nor exposing the patients to undue risk of disease progression. Such an approach could preserve quality of life and achieve significant cost savings without impairing cure rates. The ongoing Prostate Cancer Intervention Versus Observation Trial (PIVOT) is examining the utility of initial observation in a randomized trial[58], with results expected in approximately five years.

Recently, investigators at Johns Hopkins University and University of Toronto have sought to define a low risk population of patients using the standard staging tools of PSA, biopsy Gleason score, and ultrasound stage. For example, Sunnybrook Hospital in Toronto reported on a cohort of 206 low risk patients with median follow-up of 29 months [59]. Low risk men were defined as stage T1b-T2b, N0, M0, with PSA < 15 and Gleason score ≤7. Patients were evaluated every three months for the initial 24 months, and thereafter every six months. Lab testing for PSA, prostatic acid phosphatase (PAP), and serum creatinine was performed at each visit, and patients received a digital rectal exam. Transrectal ultrasound was performed every six months, and repeat transrectal 18 gauge needle biopsy was performed 12 to 18 months after study enrollment. Patients with progressive disease were counseled to stop the trial and undergo definitive surgical or radiation therapy. Progressive disease was defined as either clinical (symptoms of urethral obstruction requiring transurethral resection of the prostate, or evidence –

radiological or clinical - of metastasis), histologic (Gleason score  $\geq 8$  on the repeat biopsy), or biochemical (the three simultaneous conditions of PSA doubling time  $< 2$  years, final PSA  $> 8$  and  $p < 0.05$  on regression analysis of the time derivative of  $\ln$ PSA). In this study 137/206 patients remained on study without evidence of disease progression. Of the 69 patients who discontinued the study, only 36 (17%) had evidence of disease progression – 15 had clinical progression (5 underwent transurethral prostatic resection, and ten had an enlarging nodule on DRE), 16 had PSA progression and five had histologic progression. Of the remaining patients, 23 voluntarily withdrew, six were withdrawn for protocol violations, and four died of other causes. No patient had evidence of metastasis.

A second trial reported 23 month median follow-up of 98 men with inclusion criteria of Gleason score  $\leq 6$ , less than three of six biopsies containing cancer, no more than 50% involvement of any biopsy, and PSA density  $< 0.15$  ng/ml[60]. Patients were followed at yearly intervals with %free PSA and digital rectal exam. At two years, transrectal ultrasound was performed with 12-core diagnostic needle biopsy. Definitive treatment was recommended if Gleason pattern 8-10 histology was seen,  $> 2$  biopsies were positive for cancer, or if there was  $> 50\%$  involvement of any biopsy with cancer. Twenty-five of the 81 men (31%) had disease progression at two years. Of these men, 13 underwent radical prostatectomy and 12 of these men had potentially curable cancers ( $>70\%$  survival at 10 years expected based on pathologic features). The higher rate of progression seen in this trial was most likely an artifact of requiring only sextant biopsies, which allowed higher grade disease to be missed more often at the time of initial biopsy[61]. There was no difference in initial PSA, percent free PSA, PSA density or PSA velocity comparing patients with progression on re-biopsy to those without progression.

These data support the safety and feasibility of our proposed prostate cancer intervention trial. The articles cited demonstrate that definitive treatment for prostate cancer is possible at the first sign of progressive disease, and that with appropriate entry criteria, no man will be denied the opportunity for treatment with curative intent by participating in our study

### **3. On-study guidelines, study design**

#### **3.1 General study design**

We propose a randomized placebo-controlled trial of lycopene and fish-oil supplementation among men with newly-diagnosed, favorable-risk prostate cancer who opt for watchful waiting as their primary treatment strategy. Our main outcome will be changes in gene expression in prostate tissue biopsies taken before and after the three-month intervention period. Men will provide dietary surveys and records prior to each biopsy (i.e. before and after the three-month intervention). Serum levels of lycopene and omega-3 fatty acid will be measured before and after the intervention to assess compliance and to conduct correlative analyses.

#### **3.2 Outcome measures**

##### **3.2.1 Primary outcome measures**

The twofold decrease in mRNA transcript level detected by Taqman quantitative polymerase chain reaction comparing baseline to three-month normal prostate biopsies will be the primary outcome measure. Histologic examination of the needle biopsy tissue will be used to verify that RNA is prepared only from normal prostate areas. (Where possible, areas of tumor histology will be assessed in parallel, though assays based on these tissues will not form part of the primary outcome measure). We will specifically assess the effect of lycopene supplementation on *IGF-1* and the effect of fish oil supplementation on *Cox-2* when compared to the placebo control group.

##### **3.2.2 Secondary efficacy outcome measures**

- 3.2.2.1 The secondary aim of identifying genes correlated with nutritional supplementation with lycopene or fish oil will be accomplished by analyzing gene expression of 30,000 human genes using a cDNA array. Identification of a gene cluster associated with lycopene or fish oil but not placebo will be

accomplished using hierarchical clustering[62], or alternate algorithms that use permutation t-test statistics to account for the multiplicity of tests accomplished using such large scale microarrays[63]. If sufficient nucleic acid samples remain after primary outcome measure assessment, and microarray analysis, confirmatory Taqman quantitative polymerase chain reactions will be used to confirm the specific induction of genes identified in these studies by lycopene or fish oil.

- 3.2.2.2 To accomplish the secondary aim of identifying genes correlated with baseline dietary intake, patients will be stratified for high and low intake of total energy, fat/meat/animal products, dairy/calcium, fish, vegetables, tomatoes/lycopene, vitamin E, and selenium as defined by the Willett Semi-quantitative Food Questionnaire. Separate microarray data analyses will be performed for each dietary factor by placing all patients with low intake ( $\leq$  median) into the first half of the data table, and subsequently all patients with high intake ( $>$  median). The same standard microarray hierarchical clustering and permutation t-test approaches as in 3.2.2.1 will then be used to identify genes whose expression differs between these groups.
- 3.2.2.3 We acknowledge that the study is underpowered to assess effects of nutrition supplementation on progression rates, given the heterogeneous nature of prostate adenocarcinoma. Nevertheless, it is compelling to perform exploratory data analysis to examine whether exploratory analysis may detect genes correlated with progression or lack of progression at 12 months in the MENS study. If any correlates are detected, they will be used to formulate a hypothesis for testing in further large scale studies, such as the multi-institutional CALBG or SWOG watchful waiting trials.
- 3.2.2.4 With watchful waiting, approximately 25% of patients will experience disease progression when assessed 12 months after study entry. To assess whether the

intervention arms are different in outcome, an analysis for efficacy will be performed after 10 patients have been accrued to each of the 3 treatments and followed for 12 months from study entry. If more than 5 of the 10 patients on either supplement arm experience disease progression at twelve months, the study will be closed to further accrual. It is anticipated that this analysis will occur 15 months after the study is opened when approximately 45 patients have been entered on study. A statistician in the UCSF Comprehensive Cancer Center not associated with the design or final analysis will conduct the interim analysis. Similar analysis will be performed when the trial has reached its total accrual goal.

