### 5.2 Written description of drug dosing

Patients will take placebo, lycopene or fish oil supplements daily, as oral preparations, on an outpatient basis. The investigational pharmacy at the Cancer Center will maintain an excel

spreadsheet which will record the number and type of placebo, fish oil and lycopene capsules dispensed. In addition, to counter the possibility that different vitamin preparations could affect study results, patients will be asked to cease their usual vitamin intake and use a standard multivitamin (that we will provide). Patients must refrain from taking any other supplements, herbs, or other treatments during the 3-month intervention period.

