For the secondary specific aims (aims 1.2 through 1.4 defined above), we will consider a microarray dataset with measurements for 30,000 genes. For this exploratory investigation genes will be treated as being independent so as to first identify all possible genes that may indicate an effect due to the nutritional supplement (Aim 1.2) or to other dietary components (each considered as a binomial variable) (Aim 1.3). Fisher's exact test will be used to determine which genes result in differences in proportions with up or down regulated genes between groups. No adjustment for multiple comparisons will be made. Also, after all patients have had the potential to be followed for at least one year, they will be classified as to whether they had experienced disease progression within 1 year from protocol entry. The same exploratory techniques described above first using the baseline gene expression profile will be carried out to identify genes that may be associated with disease progression (Aim 1.4). Even though any nutritional supplement will be stopped at 3 months from the start of protocol therapy and the duration of any effect is unknown, this analysis will be repeated using the 3-month gene expression profile to identify the effects of any gene that might have been modified by protocol treatment. To account for genes with highly variable expression regardless of study arm, genes whose expression levels change two-fold in more than 20% of men on placebo (comparing three-month to baseline) will

be excluded from subsequent consideration. This might exclude possible predictors of outcome, but if there is variability within the placebo group then the results may be biased. This refining process will isolate potential predictors of nutritional change when assessing the primary as well as the secondary outcomes. Standard microarray gene expression software algorithms will facilitate analyses to determine if there are individual genes or clusters of genes associated with either supplement, dietary component or disease progression[62, 63] . Fisher's exact test will be used to determine which genes result in statistically significant differences between the groups.

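### Aim 1.2 has no single gene-selection rule: section 3.2.2.1 and section 13 name different methods, and the two-fold count in section 13 leaves direction undefined and costs power

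*Protocol*

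**What the plan says.** Section 3.2.2.1 describes the target of Aim 1.2 as "Identification of a gene cluster associated with lycopene or fish oil but not placebo". It offers two routes joined by an or: hierarchical clustering, or "alternate algorithms that use permutation t-test statistics to account for the multiplicity of tests". It does not state the contrast, or whether the quantity analysed is each man's change from baseline.

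Section 3.2.2.2 reuses the same tools for the dietary aim and says there that the "approaches as in 3.2.2.1 will then be used to identify genes whose expression differs between these groups".

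Section 13 gives another rule for Aims 1.2 and 1.3: Fisher's "exact test will be used to determine which genes result in differences in proportions with up or down regulated genes between groups". It repeats near the end of the same paragraph that Fisher's test between groups decides which genes are significant. It also says that standard array algorithms, citing the same two references as 3.2.2.1, will help the analysis. Before testing, it drops any gene that changes two-fold in more than 20% of placebo men. It calls the work exploratory and makes no multiplicity adjustment.

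**The concern.** An analyst following 3.2.2.1 could build the gene list from a cluster diagram, from a permutation t-test, or, following section 13, from Fisher tests on two-fold counts. These will give different lists from the same 30,000 genes, and the protocol does not say which one is the result.

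Direction is the second problem. If a man counts as an event when a gene moves two-fold either way, a supplement that lowers the gene adds decreases but also removes the increases that occur by chance. The two partly cancel in the pooled count. Section 2.1 also describes the outcome as a two-fold change up or down, so pooling is a natural reading, though not a stated rule.

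What is at stake is the yield of the screen. Objective 1.2 is the protocol's route to new candidate targets, and a weak rule misses real ones.

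**Working it through.** **1. The protocol's own figure.** Section 13: 20% v 60%, 29 per arm, directional .025, power 81%. Full enumeration of Fisher's exact test gives 83.0%; the continuity-corrected formula gives 28 per arm. 87/0.9 = 96.7, so 97 accrued. The design figure reproduces. The protocol gives no power figure for the gene screen.

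**2. Do shared changes pass under section 13?** Take the same two-fold rate in both arms, 29 per arm, two-sided .05 per gene (assumed; none is stated). Fisher's test flags the gene 0.1% to 2.5% of the time for shared rates of 5% to 60%, and at most 1.1% once the placebo filter is applied. They do not pass above the nominal level.

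**3. Power of the counts.** Assumptions: log changes are normal with equal SD in both arms; one-sided .025, borrowed from the primary test. Worked case, 5% up and 5% down on placebo, 30% down on supplement:

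- Two-fold threshold in SD units: z = 1.645.
- Shift on supplement: d = 1.645 − 0.524 = 1.120 SD.
- Increases left on supplement: 1 − Φ(1.645 + 1.120) = 0.3%.
- Pooled: 10% v 30.3%, Fisher power 36%.
- Decreases only: 5% v 30%, Fisher power 61% (60.5%).
- t-test on signed change: non-centrality 1.120 × √(29/2) = 4.27 on 56 df, power 99% (98.7%).

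**4. The placebo filter.** 20% of 29 is 5.8, so a gene goes out at 6 or more placebo men. With 10% of placebo men changing, P(5 or fewer of 29) = 93.6%; about 6% of such genes are removed. With 20% changing it is 46.3%; about 54% are removed.

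**5. Range.** The same formulas, before the filter and (last two columns) detected after it:

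| Placebo up/down | Supplement down | Pooled | Decreases | t-test | Pooled, after filter | Decreases, after filter |
|---|---|---|---|---|---|---|
| 5%/5% | 20% | 10% | 22% | 85% | 10% | 22% |
| 5%/5% | 30% | 36% | 61% | 99% | 36% | 59% |
| 5%/5% | 40% | 68% | 88% | >99% | 68% | 84% |
| 10%/10% | 40% | 31% | 68% | 97% | 26% | 38% |
| 10%/10% | 60% | 84% | 98% | >99% | 46% | 46% |

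For the t-test in the 30% row, the filter can take away at most 6.4 points, so at least 98.7 − 6.4 = 92.3% remains.

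**6. When pooling is harmless.** If nothing goes up in either arm, the pooled and decrease-only counts are the same: 20% v 60% gives 83% both ways.

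**The case against.** The strongest reply is that the protocol already has a between-arm comparison. Section 13 states a Fisher test between groups twice, and 3.2.2.2 describes the tools of 3.2.2.1 as finding differences between groups. That stands.

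A reader might infer from the words but not placebo in 3.2.2.1 that a gene is selected when it is significant within a supplement arm and not significant within placebo. Changes common to all arms would then be reported as supplement effects, the more so because all "patients will be asked to cease their usual vitamin intake and use a standard multivitamin". With within-arm power π, such a rule would pick an equally shared change with probability π(1 − π), at most 25% per supplement and about 38% for either. But the protocol specifies no within-arm tests. The phrase names a target, and those percentages belong to a rule that the documents do not contain.

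Pooling is also only one reading of up or down regulated, and section 8.2 describes the permutation t-test as identifying genes regulated in either direction, so one of the named tools keeps the sign. That stands too: pooling is a risk left open by the wording.

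The placebo filter shrinks the contrast for genes with much two-way movement on placebo; at 10%/10% and 60% down it removes the difference altogether. It does little at 5%/5%.

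Finally, the aim is exploratory, confirmatory PCR is planned if sample remains, and coding detail may sit in an analysis plan not shown. This limits the weight of the point. It does not reconcile two sections that name different selection methods.

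**Conclusion.** The point holds as an inconsistency with a measurable cost. Sections 3.2.2.1 and 13 do not name one selection rule for Aim 1.2; clustering alone is not a between-arm test; and the Fisher count leaves direction open. Reducing each man's change to a two-fold count loses power, and pooling the directions loses more: about 36% pooled, 61% for decreases only and 99% for the signed change in the worked case.

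These figures rest on normal changes with equal SD, 29 evaluable men per arm, an assumed one-sided .025 per gene, and up and down rates that the protocol does not give. Normal data favour the t-test, so the gap could be smaller with heavy-tailed array noise.

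The documents do not support the stronger conclusions that Aim 1.2 lacks any test of a difference, that shared changes pass as supplement effects, or that directional genes are generally lost. No primary result, sample size or stopping rule is affected.

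**What to change.** - In 3.2.2.1, replace "Identification of a gene cluster associated with lycopene or fish oil but not placebo" with: genes whose baseline-to-3-month change differs between the supplement arm and placebo.
- In section 13, name one selection test for Aim 1.2: the permutation t-test on each man's signed log change, each supplement v placebo. Section 3.2.2.1 already names this method.
- State that hierarchical clustering is used only to display the genes so selected.
- If two-fold counts are kept, count increases and decreases as separate outcomes.

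The cost is wording in two sections, with the same biopsies and array data. The one downside is that separate counts double the number of count tests, if counts are kept.
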